### Study procedures and data collection

Data will be collected through cord blood samples, ultrasound measurements, and clinical assessments.

For all patients who consent to participate in the study, an ultrasound examination will be performed within 48 hours before delivery. This ultrasound assessment includes:

a. Measurement of the fetus’s anthropometric dimensions and estimation of fetal weight.b. Evaluation of blood flow using the pulsatility index (PI) in the UA, UtA, DV, and MCA.

After birth, in both the study and control groups:

A 1.5 ml blood sample will be collected from the clamped part of the umbilical cord:a. Immediate analysis: 0.5 ml of the cord blood will be sent immediately to the laboratory to determine pH, BE, and lactate levels in the umbilical cord blood analysis.b. S100B protein analysis: The remaining 1 ml of cord blood will be placed in a labeled tube (including the mother’s name, child’s gender, date of birth, and date of collection) and sent to the laboratory for centrifugation. Serum samples will be frozen at −20°C and stored. Once approximately 80 samples are collected, the serum will be thawed and analyzed for S100B protein concentration. Any remaining material after laboratory processing will be properly disposed of.Data will be collected on gestational age, duration, and mode of delivery, along with any complications encountered during delivery. Additionally, details regarding the newborn’s condition after birth will be recorded, including gender, Apgar score, and anthropometric measurements. Observations made during hospitalization will also be documented, with particular attention to any concerning symptoms related to the CNS, such as muscle tone abnormalities or seizures.A transfontanelle ultrasound examination will be performed to assess for any abnormalities in the newborn.

Study participation does not alter standard hospitalization procedures or duration. Furthermore, collecting a blood sample for the planned tests will not interfere with cord blood collection if the mother intends to bank it.

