### Study setting

The study is being conducted at the Institute of Mother and Child in Warsaw, specifically within the Department of Obstetrics and Gynecology and the Department of Neonatology and Neonatal Intensive Care, both of which function as tertiary referral units. The center manages approximately 50 full-term newborns diagnosed with FGR annually. Recruitment commenced in June 2024 and was initially projected to continue for approximately 18 months, through December 2025, with the actual duration dependent on the number of FGR patients enrolled during that period. Complete data collection is expected to be finalized within three months of the end of recruitment (March 2026), with initial results anticipated in June 2026. At the time of protocol publication, the authors anticipated potential minor delays in patient recruitment due to a lower-than-expected incidence of pregnancies complicated by FGR at the study center, as well as a higher-than-anticipated number of exclusions. As of September 2025, approximately two-thirds of the targeted patient population have been enrolled in both the study and control groups.

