#### Control Group – Exclusion criteria.

Antenatal (at recruitment):Maternal conditions that may affect placental blood flow, such as smoking, use of illicit stimulant substances, pregestational diabetes, or chronic hypertension.Maternal depression requiring pharmacological treatment (e.g., SSRIs).Risk factors for intrauterine HI, including abnormal fetal blood flow parameters on ultrasound, abnormal CTG recordings, or the need for intrauterine transfusion (IUT).Intrapartum:Indicators of possible intrauterine infection, such as amniotic fluid leakage for more than 15 hours, spontaneous preterm delivery, diagnosed intrauterine infection, or maternal symptoms of infection.Risk factors for perinatal HI.Prolonged labor lasting more than 15 hours (counted from the onset of regular uterine contractions).Birth weight below the 10th percentile or above the 90th percentile.Apgar score less than 8 at the 1st, 3rd, 5th, or 10th minute of life.Abnormal umbilical cord blood gas analysis results, defined as pH < 7.15 or BE < −9.3 mmol/l.Postnatal:Neonatal anemia requiring a top-up transfusion within the first 24 hours of life.

The exclusion criteria for the study and control groups differ based on the principle that the control group should consist of healthy neonates without risk factors for HI. In contrast, the study group includes infants diagnosed with FGR, who inherently have a higher risk of complications. These complications, such as a low Apgar score, abnormal umbilical cord blood gas analysis parameters, or an abnormal CTG recording, are precisely the factors that serve as exclusion criteria for the control group. This approach ensures that the control group provides a valid baseline for comparison against the at-risk study group.

In patients with a singleton, full-term pregnancy who present to the labor and delivery unit and meet the inclusion criteria, without meeting the antenatal exclusion criteria (except for those related to FGR), informed written consent for testing is obtained prior to delivery. The mother is also informed that if any exclusion criteria are identified during or after delivery, the child will be disqualified from further participation in the study.

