### Sample size

The estimated minimum total sample size for the study is 120 patients, with 60 participants in each group. The planned sample size was determined for a two-sided comparison between two independent groups, assuming a significance level of 0.05, statistical power of 80%, and equal group sizes. The variability of the primary biomarker (S100B) was estimated based on data from a previously published reference study [12], which reported median values together with the 10th and 90th percentiles. As standard deviations were not provided, dispersion was approximated from the reported percentiles under an approximate normality assumption, following established methods for recovering variability from limited summary statistics [26,27]. In the reference study, the observed difference between group medians was 1.15. However, since group allocation in that study was performed retrospectively on the basis of cranial imaging findings (brain injury vs. no brain injury), a conservative approach was adopted in the present sample size estimation to minimize the risk of effect size overestimation. Therefore, the target detectable difference was defined as 50% of the previously reported median difference.

Based on these assumptions, the estimated required sample size was approximately 55 participants per group. Additionally, considering that up to 10% of collected samples could be non-diagnostic or otherwise non-evaluable, the planned recruitment target was increased to 60 participants per group (120 participants in total). Sample size calculations were performed using standard power analysis procedures implemented in G*Power software (version 3.1.9.4).

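### S100B will be assayed in at least two runs (about 80 samples, then about 40), but the stated primary test ignores assay run and nothing stated requires group balance within runs

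*Protocol article*

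**What the plan says.** Under Study procedures and data collection, serum is frozen at −20 °C and stored. The assay rule is "Once approximately 80 samples are collected, the serum will be thawed and analyzed for S100B protein concentration". The same paragraph says that whatever is left after laboratory processing is disposed of.

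Under Sample size: "The estimated minimum total sample size for the study is 120 patients, with 60 participants in each group". The calculation is two-sided, "assuming a significance level of 0.05, statistical power of 80%, and equal group sizes". It arrives at about 55 per group, raised to 60 for samples that cannot be evaluated.

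Under Statistical methods, S100B is compared between groups by Student's t-test if it is normally distributed and by the Mann-Whitney test otherwise. Covariates appear only for the regressions relating S100B to other continuous variables. Those named, as examples, are pregnancy duration and mode of delivery.

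Under Study setting, about two-thirds of the target had been enrolled in both groups by September 2025, with recruitment still open. The article does not say how samples after the first 80 or so are to be assayed.

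**The concern.** An assay threshold of 80 in a study of 120 means that the primary endpoint is not measured on one occasion. Separate runs of the same assay can differ in level, and first-run and second-run samples may also differ in time spent frozen. A level difference between runs enters the S100B values directly.

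The stated primary test has no place for run. If both groups contribute the same share of their samples to each run, the shift cancels from the group difference but stays in the within-group spread, so power falls. If the shares differ, part of the shift appears as a difference between FGR and control infants. Because leftover serum is discarded, the laboratory cannot settle the matter later by assaying old and new samples together. It has to be handled by how the remaining samples are allocated to runs and by the analysis.

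**Working it through.** **Inputs from the protocol article.** Assay threshold about 80 samples (Study procedures and data collection). Planned total 120, 60 per group; two-sided α 0.05; power 80%; about 55 per group required; target difference half of the reference median difference of 1.15, that is 0.575 (Sample size).

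**Assumptions.** The article gives no assay precision, so between-run shifts *b* of 0.5 and 1 SD are assumed. The SD is not stated either.

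**1. The plan's own figure.** Without the SD, 55 per group cannot be reproduced independently. It can only be solved backwards: with the t distribution, n = 55 and 80% power imply a standardised difference d ≈ 0.539, that is SD ≈ 0.575 / 0.539 ≈ 1.07. This d is used below.

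**2. Number of runs.** 80 / 120 = 66.7%, leaving 120 − 80 = 40. Whether 80 is a one-time threshold or a batch size, there are at least two runs.

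**3. Groups balanced across runs.** The group difference is unbiased. A shift of *b* SD adds to the variance within each group:

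inflation = 1 + b² × (2/3) × (1/3)

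| Shift b (assumed) | Inflation | Effective d = 0.539 / √inflation | Power, 55 per group |
|---|---|---|---|
| 0 | 1.000 | 0.539 | 80.0% |
| 0.5 SD | 1.056 | 0.525 | 77.8% |
| 1 SD | 1.222 | 0.488 | 71.7% |

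Simulation with all 60 per group evaluable, an exact 40/40 then 20/20 split and no run term gives power of about 0.82 at 0.5 SD and 0.78 at 1 SD, against 0.83 with no shift. Type I error is 0.043 and 0.031, so the unadjusted test becomes conservative and does not give excess false positives.

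**4. Groups not balanced across runs.** The bias in the group difference is

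bias = b × (share of FGR samples in run 2 − share of control samples in run 2)

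To show how the formula works, and not as an expected value: a first run of 32 FGR and 48 control samples leaves 28 and 12 for the second. The shares are 28/60 = 0.467 and 12/60 = 0.200, a difference of 0.267. With b = 0.5 SD the bias is 0.267 × 0.5 = 0.133 SD, and the simulated type I error is 0.101. A milder 36/44 first run leaves 24 and 16, so the bias is 0.5 × (24 − 16)/60 = 0.067 SD and the simulated type I error is 0.057.

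**5. With a run term.** The shift is estimated and removed, both from the group difference (step 4) and from the residual spread (step 3), at the cost of one degree of freedom.

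**The case against.** The strongest reply is that the harm is small and conditional. Enrolment stood at about two-thirds in both groups, which points to a first run near 40/40. In that case there is no bias, and with 60 evaluable per group an assumed 0.5 SD shift still leaves power above 80%. No shift size is supported by the article. Plate layout, laboratory masking and run adjustment are also details that a journal article often leaves to fuller documents. Much of this stands, and it limits the point to a modest improvement. It does not remove it: the article does state an assay schedule and a primary test, and the two do not fit together.

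A reader might go further and infer that the first run reveals the primary result at two-thirds of the information, so that recruitment or exclusions could be steered by it. The documents do not support that:

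- Thawing and measuring serum is a laboratory step. No early comparison or release of values is described, and initial results are expected only after data collection ends. Testing at 80 and again at 120, each at 0.05, would give a type I error of about 7.7%, but no such test is planned, so that figure does not describe this study.
- Recruitment length is described "with the actual duration dependent on the number of FGR patients enrolled during that period". That is accrual, not results.
- One control exclusion, "Risk factors for perinatal HI", has no list or threshold. However, most of the others have explicit limits, and exclusion data are gathered only up to discharge, normally before the infant's own S100B value exists.

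Nor is group imbalance between runs shown. Matching controls on the percentage of cesarean deliveries is not evidence of it.

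**Conclusion.** The point holds in limited form. The stated schedule produces at least two assay runs, the stated primary test ignores run, and discarding serum rules out later re-assay of the first run with the second. With balanced runs the cost is precision only: about 2 percentage points of power at 55 per group for an assumed 0.5 SD shift, and about 8 for 1 SD. With unbalanced runs there is bias, equal to the shift multiplied by the difference in run shares. Its size cannot be predicted from the article, and the 0.133 SD above only illustrates the formula. The power figures rest on the assumed shifts and on a standardised difference solved backwards from the stated 55 per group. This is an inexpensive improvement to make, not a flaw that invalidates the study.

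**What to change.** - State how the samples after the first 80 or so are assayed, and include FGR and control samples in equal proportion in each remaining run.
- Stratify or adjust the primary comparison for assay run: a linear model with group and run if S100B is normally distributed, or a van Elteren stratified rank test if it is not. Add run to the secondary regression models.
- As a low-cost safeguard, withhold S100B values from the recruiting team until recruitment and exclusions are final.

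The cost is a laboratory instruction, a primary test slightly more complex than the one named, and one degree of freedom. The run adjustment and the balancing of later runs remain possible even if the first run has been done. Assaying all samples together after recruitment closes is optional: it would avoid the run split, but it lengthens storage at −20 °C and, given enrolment in September 2025, may no longer be possible.

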### Criteria for discontinuing participation

If a full ultrasound flow assessment becomes unfeasible due to technical issues, advanced labor, or urgent delivery indications, it will be halted. However, any partial data collected will still be analyzed.

If an umbilical cord blood sample cannot be collected after birth, the patient will be excluded from the study. Nevertheless, data from excluded patients will be retained to support further analysis and ensure a comprehensive statistical evaluation.

In cases where consent is withdrawn, any data collected up to that point will be retained and used in the study.

### Compliance

Before the study commenced, a meeting was held to familiarize the researchers and staff with the study protocol. The protocol was presented in detail, including the rationale behind the study. Additionally, schematic instructions were provided, covering patient qualification, the required tests for qualification, and the intervention procedures.

The medical records of participating patients are clearly labeled to ensure adherence to the study protocol. Each patient’s medical record includes a schematic outlining the inclusion and exclusion criteria.

### Explanation for the choice of comparators

Biomarkers associated with the risk of hypoxia-related CNS injury should meet several key criteria:

They should be detectable in easily accessible fluids such as blood, amniotic fluid, or urine, allowing for straightforward sample collection.They should identify patients at risk before symptoms emerge or clinical examinations, or other tests (e.g., ultrasound, MRI, or EEG) reveal any abnormalities.They should provide a quantitative measure of the severity of perinatal hypoxic stress.The tests should be simple, quick, cost-effective, and characterized by repeatability, sensitivity, and specificity [25].

To date, few markers have been thoroughly evaluated for each of these criteria. However, the S100B protein shows promise as a potential marker. It can be detected in blood, saliva, urine, and amniotic fluid, potentially allowing for the early identification of neonates at risk of adverse neurodevelopmental outcomes in a relatively quick and inexpensive manner. Nonetheless, additional prospective studies are needed.

### Outcome measures

The study’s primary endpoint will be the concentration of S100B protein measured from a cord blood sample taken after birth in both the study and control groups.

Additional endpoints will include:

The potential correlation between S100B concentration and pH, BE, and lactate levels, as determined in the cord blood gas analysis in both the study and control groups.The possible relationship between cord blood S100B protein concentration and blood flow parameters (PI) in the UA, UtA, DV, and MCA, as assessed by fetal ultrasound performed within 48 hours before delivery.

### Participant timeline

For the primary endpoint data acquisition, the study period includes the fetal ultrasound examination conducted 48 hours before delivery and the delivery process itself. This encompasses umbilical cord clamping, collecting cord blood from the severed portion of the umbilical cord, and recording anthropometric measurements. Additional data that may lead to patient exclusion (e.g., diagnosis of intrauterine infection or neonatal anemia requiring a top-up transfusion in the control group) or that could impact the study results (e.g., transfontanelle ultrasound findings or abnormal neurological symptoms) will be collected until the child is discharged from the hospital. The overall study design and timeline are presented in Fig 1.

**Fig 1 pone.0355156.g001:**
[figure not shown]
Participant timeline according to the SPIRIT 2025 guidelines. Schedule of enrollment, data collection, assessments, and follow-up procedures in the prospective cohort study evaluating cord blood S100B protein concentration as a potential biomarker associated with fetal hypoxia in late fetal growth restriction. The timeline presents study procedures from screening and enrollment through baseline assessment, perinatal data collection, neonatal assessments, sample processing, data entry, and final statistical analysis. T0 indicates baseline assessment; T1–T5 represent subsequent study time points (T1: 48 hours after delivery, T2: birth, T3: hospital discharge or 2–14 days, T4: 3 months, T5: 6 months). X indicates the time point of assessment or data collection; arrows indicate ongoing procedures or follow-up periods.

### Sample size

The estimated minimum total sample size for the study is 120 patients, with 60 participants in each group. The planned sample size was determined for a two-sided comparison between two independent groups, assuming a significance level of 0.05, statistical power of 80%, and equal group sizes. The variability of the primary biomarker (S100B) was estimated based on data from a previously published reference study [12], which reported median values together with the 10th and 90th percentiles. As standard deviations were not provided, dispersion was approximated from the reported percentiles under an approximate normality assumption, following established methods for recovering variability from limited summary statistics [26,27]. In the reference study, the observed difference between group medians was 1.15. However, since group allocation in that study was performed retrospectively on the basis of cranial imaging findings (brain injury vs. no brain injury), a conservative approach was adopted in the present sample size estimation to minimize the risk of effect size overestimation. Therefore, the target detectable difference was defined as 50% of the previously reported median difference.

Based on these assumptions, the estimated required sample size was approximately 55 participants per group. Additionally, considering that up to 10% of collected samples could be non-diagnostic or otherwise non-evaluable, the planned recruitment target was increased to 60 participants per group (120 participants in total). Sample size calculations were performed using standard power analysis procedures implemented in G*Power software (version 3.1.9.4).

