### Statistical methods

Descriptive statistics, including percentages for categorical variables and mean values, standard deviations, medians, and interquartile ranges for continuous variables, will be used to summarize the data. The Kolmogorov-Smirnov test, along with graphical analysis, will be employed to assess whether continuous variables conform to a normal distribution.

For analyzing the relationship between a quantitative variable and a qualitative variable (e.g., comparing S100B levels between the study and control groups), the Student’s t-test for independent samples will be used if the continuous variable is normally distributed. If the continuous variable does not meet the assumptions of normality, the Mann-Whitney U test will be applied instead.

To test hypotheses about the relationships between two continuous variables (e.g., S100B protein concentration versus flow rates), while accounting for confounding factors such as pregnancy duration and mode of delivery, either multivariate quantile regression or multivariate linear regression will be employed, depending on the distribution of the outcome variable.

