## Study strengths, limitations and future directions

To address the knowledge gap, the study aims to answer the following questions:Is cord blood S100B protein concentration significantly higher in infants with prenatally diagnosed late FGR, a condition associated with increased risk of hypoxic CNS injury?Does the concentration of S100B protein in umbilical cord blood correlate with blood flow parameters in the UA, UtA, DV, and MCA, as assessed by ultrasound within 48 hours before delivery?Is there an association between S100B protein concentration and pH, BE, and lactate levels in cord blood, in the context of evaluating perinatal hypoxic stress?The study procedures are straightforward and confined to a specific time point, which facilitates the accurate implementation of the study protocol.The study evaluates only short-term outcomes and does not account for the long-term neurological development of the children.In cases of urgent indications for delivery or an advanced stage of labor at admission, performing a reliable Doppler flow assessment may not be feasible.In some instances, collecting the necessary volume of cord blood for testing may be difficult due to technical problems.Due to numerous exclusion criteria in both the control and study groups, which may arise after informed consent is obtained, some patients may be disqualified during the study.

The present study may serve as a starting point for further investigations into the usefulness of S100B protein as a biomarker associated with the risk of hypoxia-related CNS injury in neonates with late FGR. Future research should consider extending the diagnostic approach to include long-term neurological follow-up, as well as additional assessment of cerebral blood flow using postnatal ultrasonography and monitoring of cerebral bioelectrical activity with amplitude-integrated electroencephalography (aEEG). Such an approach could enable evaluation of the relationship between perinatal S100B protein concentrations and subsequent neurodevelopmental outcomes in children with FGR.

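### Sixty per group does not quite carry the plan's own 10% allowance: 55 evaluable needs 62 sampled per group, and 60 leaves 54 (about 79% power)

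*Protocol article*

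**What the plan says.** The Sample size section describes a calculation "determined for a two-sided comparison between two independent groups", "assuming a significance level of 0.05, statistical power of 80%, and equal group sizes". In the reference study "the observed difference between group medians was 1.15", and for this trial "the target detectable difference was defined as 50% of the previously reported median difference". The standard deviation was approximated from published percentiles, but its value is not given. The result is about 55 per group. The step to the recruitment target is that "up to 10% of collected samples could be non-diagnostic or otherwise non-evaluable, the planned recruitment target was increased to 60 participants per group", 120 in total, and the section opens by calling 120 the minimum.

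Other sections bear on what the 60 counts. Criteria for discontinuing participation removes a patient from whom no cord blood can be collected. The eligibility section lists exclusions that become known during or after delivery. The limitations section says that "some patients may be disqualified during the study". Study setting explains a possible recruitment delay by fewer FGR pregnancies than expected, "as well as a higher-than-anticipated number of exclusions".

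**The concern.** An allowance for loss should return at least the required number once the loss has happened. Here the required number, the loss and the target stand next to each other, and at the stated upper limit of loss they do not agree. The 80% power will be repeated in the results paper, so the number presented as a minimum should support it.

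There is also a question of what is being counted. The allowance is a fraction of collected samples, while the target is a number of participants. Between consent and a usable sample a participant can be lost for reasons other than a failed assay. If the point of counting is not stated, a reader cannot tell how many evaluable participants the 60 should yield.

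**Working it through.** **Inputs (Sample size section).** Two-sided alpha 0.05; power 80%; equal groups; required n about 55 per group; up to 10% of collected samples lost; target 60 per group; target difference 0.5 × 1.15 = 0.575.

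**The plan's own figure.** The 55 cannot be reproduced directly because the article gives neither a standard deviation nor a standardized effect. It can be back-solved. For a two-sample t-test, power is the probability that a noncentral t variable with 2n − 2 degrees of freedom and noncentrality d·√(n/2) exceeds the two-sided 5% critical value. Setting this to 80% at n = 55 gives d = 0.539, hence an implied SD of 0.575/0.539 = 1.067. The normal approximation gives an SD of about 1.076. These SDs are inferences, not figures from the article.

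**The inflation step.**
- Correct form, n/(1 − loss): 55/0.90 = 61.1, rounded up to 62 per group, 124 in total.
- Cruder form, n × (1 + loss): 55 × 1.10 = 60.5, rounded up to 61.
- What 60 delivers at 10% loss: 60 × 0.90 = 54.
- What 60 can absorb: 1 − 55/60 = 8.3%.
- Check of 62: 62 × 0.90 = 55.8, which is at least 55.

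Neither form of inflation gives 60.

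**Power at the resulting n (d = 0.539).**

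| Evaluable per group | Situation | Noncentrality d·√(n/2) | Power |
|---|---|---|---|
| 60 | no loss | 0.539 × 5.477 = 2.95 | 83.4% |
| 55 | 8.3% loss | 0.539 × 5.244 = 2.83 | 80.0% |
| 54 | 10% loss | 0.539 × 5.196 = 2.80 | 79.3% |

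The shortfall at the stated upper limit of loss is 80.0 − 79.3 = 0.7 points. The normal approximation, calibrated to 80% at 55, also gives 79.3% at 54. The shortfall depends hardly at all on the unknown SD, because the effect size is fixed by the condition of 80% at 55.

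**The case against.** The strongest reply is that the slip is one participant per group and lies within the roughness of the text. The 55 is given as approximate and the 10% as an upper limit. If the unrounded requirement were 54, then 60 less 10% would meet it exactly. At any loss up to 8.3% the stated power holds, and with no loss it is above 83%. All of this stands, and it limits the point to a small correction. It does not make 60 the right result from the two figures printed.

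Three stronger readings are tempting, and the documents do not support them.

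- **The test.** A reader might infer a further loss of power because "If the continuous variable does not meet the assumptions of normality, the Mann-Whitney U test will be applied instead". The usual efficiency penalty for that test is the one for normal data, and under normality the plan uses the t-test. With skewed data the switch can gain power: in an illustrative lognormal location shift with the same SD and difference, Mann-Whitney power at 54 per group was 92% or more. Nothing in the article says which test is likely.
- **Exclusions.** A reader might infer that post-consent exclusions come out of the 60. No section says so, and no exclusion rate is given, so any power figure would measure an assumed rate. Study setting presents the excess exclusions as a cause of delay, which fits recruitment continuing until the target is met.
- **The end date.** A reader might infer that recruitment stops in December 2025 with too few participants. Study setting calls that date an initial projection and makes the duration depend on enrolment.

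**Conclusion.** The inflation step is slightly wrong. About 55 evaluable per group with up to 10% of collected samples lost needs 62 sampled per group; 60 leaves 54. The cost is about 0.7 points of power at the full 10% loss (79.3% against 80%), and nothing at losses up to 8.3%. This rests on a two-sample t-test and on an effect size back-solved from 55.

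It would be too strong to say that the trial fails to deliver its 80% power. That is true only at the upper limit of the allowance, by less than one point, and against a requirement stated as approximate. Design, analysis and interpretation are unaffected. What the 60 counts is a matter for clarification: the allowance refers to collected samples and does not mention the other routes out of the study, but no loss of power from those routes is shown.

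**What to change.** Restate the figures in the Sample size section in one of two ways:

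- keep 60 sampled per group and say that this gives about 79% power if 10% of samples are non-evaluable, and 80% if the loss is up to 8% (60 × 0.92 = 55.2); or
- state 62 sampled per group (124 in total) as the number that leaves 55 evaluable at 10% loss.

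In the same sentence, say that the number counts participants with a collected cord blood sample who remain after the intrapartum and postnatal exclusions. This agrees with the account of recruitment in Study setting.

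The first option costs only a change of text and a slightly less favourable power statement. The second adds four participants in total (124 − 120), at a centre that already reports slower recruitment than expected. Neither changes a study procedure or the analysis.
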